### Study hypotheses

2.2

**
*Primary objective:*
** MRI measurements of tumour hypoxia levels directly correlate to measurements of [^18^F]MISO PET uptake.

**
*Secondary objective 1:*
** MRI measurements of hypoxia in the tumour volume acquired in the test-retest scans have excellent repeatability.

**
*Secondary objective 2*
**: Dose-painting radiotherapy plans that target areas of hypoxic tumour with high doses of radiation will result in improved modelled local tumour control probability and minimal alteration to normal tissue dose tolerances compared to standard radiotherapy plans.

**
*Secondary objective 3*
**: MRI measurements of tumour hypoxia at 12 weeks post chemoradiation treatment completion spatially overlap with sites of local recurrence and negatively correlate with patient overall survival time.

**
*Secondary objective 4*
**: Increases in measurements of tumour hypoxia observed during chemoradiation treatment negatively correlate with patient overall survival time.

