#### Primary objective

2.3.1

Spatial correlation between hypoxic tumour volume (HTV) determined with MRI and [^18^F]MISO will be evaluated via measurements of Dice similarity coefficient. Dice similarity coefficients > 0.75 will be considered a good spatial correlation. Quantitative correlation of voxel-wise and HTV-average levels of hypoxia will be evaluated via measurement of the Pearson’s correlation coefficient. Correlation coefficients > 0.7 will be considered a strong correlation (27).

#### Secondary objective 1

2.3.2

Repeatability of voxel-wise and HTV-average levels of hypoxia in the tumour, calculated as explained below for each hypoxia imaging biomarker, will be assessed via measurements of intraclass correlation coefficient (ICC). Repeatability is considered excellent, good, moderate or poor for ICC values > 0.9, 0.75-0.9, 0.5- 0.75 and< 0.5, respectively. Additionally, similarity between the HTV defined with the MRI biomarker at the two timepoints will be assessed via calculation of Dice similarity coefficient. Dice similarity coefficients > 0.9 will be considered a strong correlation.

#### Secondary objective 2

2.3.3

The predicted patient benefits of the hypoxia-guided dose-painting radiotherapy plan will be compared with the actual patient outcomes following conventional treatment, by using metrics including modelled tumour control probability (TCP) and toxicity measurement to organs at risks and healthy brain (including equivalent uniform dose). Voxel-wise dose-painting prescriptions within the conventional radiotherapy targets will be escalated from 60 Gy based on the level of hypoxia determined by the selected MRI imaging biomarker according to the method previously described by Toma-Dasu et al. (28). Targets delineation and constraints to organs at risk as per ESTRO-EANO guidelines (29) will be set equally for the optimisation of the conventional and dose-painting plans. Success for this objective will be achieved if the dose-painting plans result in improved TCP by more than 15% over conventional treatment, while dose metrics to organs at risk remain similar.

#### Secondary objective 3

2.3.4

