**Figure 4 f4:**
[figure not shown]
Example of quantitative images obtained from MRI protocol acquisition on a healthy volunteer.

A region of interest (ROI) will be delineated with a semi-automated tool and checked by an experienced neuroradiologist on the T_2_-weighted image as the hyperintense regions around the tumour. The ROI will be propagated to the T_1_, T_2_, T_2_
^*^ and CBF maps. Voxel-wise and median values of R_1_, R_2_, R_2_
^*^ and CBF within the ROI will be calculated from the quantitative T_1_, T_2_, T_2_
^*^ and CBF maps, respectively. The reproducibility, repeatability and accuracy of the quantitative-MRI protocol will also be assessed using guidelines and a phantom developed by the National Institute of Standards and Technology and the International Society of Magnetic Resonance in Medicine (42).

On one hand, HTV will be defined via OE MRI as the proportion of voxels within the ROI being refractory in R_1_ for O_2_ challenge [i.e. ▵R_1_ ≤ 0, where ▵R_1_ = R_1_ (O_2_) – R_1_ (air)] and well-perfused (i.e. CBF > 0), as previously determined by experts in the field (36, 41, 43, 44). ▵R_1_ will be calculated in two ways. First, it will be calculated from the R_1_ maps obtained from the T_1_-mapping sequences acquired before [R_1_ (air)] and during O_2_ breathing [R_1_ (O_2_)]. Second, it will be calculated from T_1_ maps derived from the T_1_-weighted dynamic acquisition, such that R_1_ (air) is derived from the average of the first two R_1_ maps acquired at baseline while breathing air and R_1_ (O_2_) is derived from the last four R_1_ map acquired during oxygen breathing. ▵R_1_ values obtained with the two approaches will be compared. The approach which will provide the most reliable ▵R_1_ values in the test-retest scan across the entire patient cohort will then be selected to calculate the HTV. Voxel-wise ΔR_1_ values in the HTV will be converted into values of partial pressure of oxygen (pO_2_) using a similar approach to the one used by Chakhoyan et al. (35), which exploits known values of pO_2_ in normal appearing white and gray matter and uses these values to calibrate the pO_2_ values in the tumour. This approach will provide a way to quantitatively measure voxel-wise levels of hypoxia.

On the other hand, HTV will be defined via BOLD MRI by using a previously established method to estimate relative oxygen extraction fraction (rOEF) in human gliomas from T_2_, T_2_

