^*^ and CBV maps (37). Briefly, the transverse relaxation due to local magnetic field inhomogeneities in a blood vessel network, 
$R_{2}^{'}$
, will be calculated within the ROI from T_2_ and T_2_
^*^ maps according to Equation 1:

(1)
$$R_{2}^{'}=R_{2}^{*}-R_{2}=\left(\frac{1}{T_{2}^{*}}-\frac{1}{T_{2}}\right)$$

Then, the Yablonskiy and Haacke model will be applied to derive the oxygen extraction fraction (OEF) according to Equation 2:

(2)
$$OEF=\frac{R_{2}^{'}}{\zeta \cdot \gamma \cdot \frac{4}{3}\cdot \pi \cdot \Delta \chi \cdot B_{0}}$$

where 
ζ
 is the venous fraction of the blood network and approximately equals the venous blood volume (~0.75.CBV), 
$B_{0}$
 is the magnetic field strength, 
γ
 is the gyromagnetic ratio of value 2.675 . 10^8^ s^-1^ T^-1^, 
△χ
 is the susceptibility difference between deoxygenated and oxygenated blood 
$△\chi =△\chi_{0}\cdot Hct=0.924\cdot 10^{-7}$
, which is calculated from the susceptibility difference between fully deoxygenated and fully oxygenated hemoglobin 
$△\chi_{0}=0.264\cdot 10^{-6}$
 and the small-vessel hematocrit (Hct = 0.35). As the absolute quantification of venous CBV in patients is not feasible, the venous blood vessel fraction 
ζ
 is approximated by CBV and the remaining factors are grouped into a constant 
$c=\gamma \cdot \frac{4}{3}\cdot \pi \cdot △\chi \cdot B_{0}=317\;s^{-1}$
. Using these simplifications, rOEF can be calculated according to Equation 3:

(3)
$$rOEF=\frac{R_{2}^{'}}{CBV\cdot c}=\left(\frac{1}{T_{2}^{*}}-\frac{1}{T_{2}}\right)\cdot \frac{1}{CBV\cdot c}$$

To derive the HTV, a hypoxia rOEF threshold (rOEF_hypoxia_) will be defined from the mean, rOEF_mean_, and the standard deviation, rOEF_SD_, of the tissue within the ROI, such that rOEF_hypoxia_ = rOEF_mean_ + rOEF_SD_. Finally, the HTV will be defined by all voxels within the ROI for which rOEF> rOEF_hypoxia_. Hypoxia levels in voxels belonging to the HTV will be measured by rOEF values.

To facilitate the assessment of spatial and quantitative voxel-wise correlations in HTV and in levels of tumour hypoxia defined by the different imaging biomarkers, all MRI images will be resampled into the spatial resolution of the MRI image with the highest resolution by linear interpolation of voxel-wise intensity values.

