#### PET imaging analysis

2.7.4

PET data will be reconstructed with CT data acquired simultaneously. To quantify the radioactivity concentrations in the PET images as standardised uptake values (SUV), raw PET images will be decay corrected to the point of tracer injection using a fluorine-18 half-life of 109.77 min. PET images will be co-registered to the MRI images acquired at the same timepoint of the study via rigid co-registration of the simultaneously acquired CT image to the T_2_ map. This way the ROI delineated on the T_2_ image can be applied to the PET SUV image and be used for quantification of lesion [^18^F]MISO uptake. The primary measures to quantify lesion [^18^F]MISO uptake will be maximum standardised uptake value (SUV_max_) and tumour-to-background ratios (TBR). TBR images will be derived by normalisation of the SUV image by the mean SUV value calculated in a region of interest delineated in the contralateral healthy brain. The HTV will be defined by all voxels within the tumour ROI with a TBR ≥ 1.2 - threshold value shown to optimally distinguish hypoxic tumour from normoxic brain tissue at 90 min post tracer injection in a previous GBM study (45) – and DSC MRI-derived CBF>0 – indicating well-perfused tissue. Hypoxia levels in voxels belonging to the HTV will be measured by values of pO_2_ derived from TBR values using the above mentioned approach used by Chakhoyan et al. (35).

Finally, to facilitate the assessment of spatial and quantitative voxel-wise correlations in HTV and in levels of tumour hypoxia defined by the different imaging biomarkers, [^18^F]MISO TBR images will be resampled into the spatial resolution of the MRI image with the highest resolution by linear interpolation of voxel-wise intensity values.

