### Statistical analysis

2.10

The sample size required for this study was calculated from a power analysis performed with the software GPower v.3.1. based on the hypothesis linked to the primary objective of the study. The hypothesis is that OE and BOLD MRI measurements of hypoxia within the tumour lesion will positively correlate (Pearson correlation coefficient > 0.7) to [^18^F]MISO values of uptake. The statistical test used in the power analysis was a correlation test using a point biserial model. Based on a Pearson correlation coefficient of 0.7, which was previously reported for the correlation of MRI measurements of hypoxia and the gold-standard immunohistochemical marker of hypoxia pimonidazole (27), the minimum sample size required to answer the hypothesis with 98% power and 5% two-tailed alpha, is 19. As such, up to 20 patients will be recruited for this study. A sample size of N=20 patients, which is large compared to the usual sample size used to estimate repeatability of ROI-averaged quantitative imaging measures (46), will allow us to test the hypothesis linked to secondary objective 1 - involving assessing the repeatability of OE/BOLD MRI measurements of hypoxia with the test-retest scan - with a specificity of at least 85% with 95% certainty (47); and the hypothesis linked to secondary objective 2 – involving the assessment of whether dose-painting radiotherapy plans result in improved TCP by more than 15% over conventional treatment - with 99% power and 5% one-tailed alpha (calculated with GPower v.3.1.).

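### The primary criterion expects a positive Pearson r above 0.7 for both MRI biomarkers, but the hypoxia scales the plan defines run in opposite directions and no pairing or sign is stated

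*Protocol article*

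**What the plan says.** **Direction and threshold.** The primary hypothesis in section 2.2 is that "MRI measurements of tumour hypoxia levels directly correlate to measurements of" PET uptake. Section 2.3.1 sets the analysis: "Quantitative correlation of voxel-wise and HTV-average levels of hypoxia will be evaluated via measurement of the" Pearson coefficient, with values above 0.7 labelled strong. Section 2.10 repeats the direction for OE and BOLD MRI together, saying they "will positively correlate (Pearson correlation coefficient > 0.7) to" MISO uptake.

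**Scales.**
- OE MRI (section 2.7.2): voxel-wise ΔR1 "values in the HTV will be converted into values of partial pressure of oxygen (pO_2", and this is presented as the quantitative hypoxia level.
- BOLD MRI (section 2.7.2): "Hypoxia levels in voxels belonging to the HTV will be measured by rOEF values". The BOLD hypoxic tumour volume (HTV) consists of voxels above an rOEF threshold.
- PET (section 2.7.4): "Hypoxia levels in voxels belonging to the HTV will be measured by values of pO_2_ derived from TBR values". The same section names SUVmax and TBR as the main uptake measures, defines the PET HTV by TBR of at least 1.2, and resamples TBR images for the voxel-wise quantitative comparison.
- Sections 2.1 and 2.10 describe the PET side of the correlation as uptake.

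No section uses an absolute value of r, reverses a scale, gives a sign for each biomarker, or says which PET quantity goes with which MRI biomarker.

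**The concern.** A one-directional criterion works only if both variables rise together when the biomarker is valid. Here pO2 falls as hypoxia worsens, while rOEF and TBR rise. Applying one positive threshold to OE and BOLD against the same PET quantity therefore puts one of them on the wrong side of zero by construction.

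This is the primary objective. A valid biomarker could be reported as not meeting the stated hypothesis. Alternatively, the PET quantity and the sign could be sorted out once results are known. The choice of PET quantity may affect more than the sign: unless the conversion from TBR to pO2 is linear (the article does not give its form), Pearson's r against TBR and against pO2 will also differ in size, so the choice could move a result across 0.7.

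**Working it through.** **1. The plan's own figure.** Section 2.10 gives N = 19 for r = 0.7, 98% power, 5% two-tailed alpha and a point-biserial model. Taking the null as rho = 0 (not stated, but implied because it reproduces N), power comes from a noncentral t with df = n − 2 and noncentrality r/√(1 − r²) × √n. With r = 0.7 the first factor is 0.7/√0.51 = 0.980.

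| n | Power |
|---|---|
| 18 | 0.9737 |
| 19 | 0.9803 |
| 20 | 0.9854 |

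The smallest n reaching 98% is 19, as stated. A two-tailed test of rho = 0 is symmetric in sign, so the power is the same for rho = −0.7.

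**2. Direction of each scale.**

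| Measure | As hypoxia worsens | Basis |
|---|---|---|
| OE pO2 | falls | meaning of pO2 |
| BOLD rOEF | rises | HTV is rOEF above threshold (2.7.2) |
| PET pO2 | falls | meaning of pO2 |
| PET TBR | rises | HTV is TBR ≥ 1.2 (2.7.4) |

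SUVmax is a single maximum per lesion. It cannot enter a voxel-wise or HTV-average correlation, so the real ambiguity on the PET side is TBR against pO2.

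**3. Expected sign for each pair.** If two measures are a + b·h and c + d·h for underlying hypoxia h, Pearson's r is +1 when b and d share a sign and −1 when they do not. For ideal linear biomarkers:

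| | PET pO2 | PET TBR |
|---|---|---|
| OE pO2 | +1 | −1 |
| BOLD rOEF | −1 | +1 |

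Each column has exactly one negative entry. A single PET quantity used for both biomarkers therefore always leaves one valid biomarker with a negative expected r. The diagonal (OE pO2 with PET pO2, rOEF with TBR) is positive throughout, but the plan does not state that pairing.

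**4. Size at patient level.** Bivariate normal simulation, n = 20, 50,000 replicates per setting:

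| True \|rho\| | P(r > 0.7), aligned pair | P(r > 0.7), opposed pair |
|---|---|---|
| 0.70 | 0.54 | 0.000 |
| 0.80 | 0.85 | 0.000 |
| 0.90 | 0.995 | 0.000 |
| 0.95 | 1.00 | 0.000 |
| 0.99 | 1.00 | 0.000 |

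For the opposed pair, P(r < −0.7) equals the aligned column, so the association is just as strong and only the direction of the criterion misses it. The 0.54 in the first row is a separate matter: it arises because an observed r is compared with a threshold equal to the true value.

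These probabilities apply to HTV-average values with one pair per patient. The sign argument in step 3 applies equally to voxel-wise correlations, but the probabilities do not.

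**The case against.** **A pairing exists that removes the conflict.** OE and PET are both converted to pO2 by the same cited approach, and TBR images are separately resampled for quantitative comparison. OE pO2 could be set against PET pO2 and rOEF against TBR, giving positive expected r in both cases. This is correct, and it means the inversion is not inevitable. But section 2.7.4 defines the PET hypoxia level as pO2 without restricting it to OE, and sections 2.1 and 2.10 name uptake for both biomarkers. The pairing is a sensible repair that the text does not contain.

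**The hypothesis concerns hypoxia levels, and a low pO2 is a high level.** On that reading the scales are implicitly aligned. However, the plan says the levels are measured by pO2 and by rOEF and states no inversion.

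**The 0.7 threshold is only a strength label.** This stands. A reader might infer that a well-performing biomarker would be declared a failure. The article does not say so: it attaches no pass/fail consequence to the primary correlation, whereas secondary objective 2 does have an explicit success rule. An analyst who saw rOEF and PET pO2 at r = −0.8 would probably recognise agreement.

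**The test is two-tailed and N is unaffected.** This also stands, as does the point that the correct sign of every pair can be derived in advance, which limits the room for post hoc choice once the pairing is fixed.

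**Sign conventions can be left to a full protocol or SAP.** An omission alone would not be a finding. Here the article states a direction and a set of scales that cannot all hold together for a common PET measure.

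**Conclusion.** The point holds as an internal contradiction in the primary quantitative criterion. If one PET quantity serves both MRI biomarkers, one valid biomarker has a negative expected r and cannot meet the criterion as worded: BOLD rOEF if the quantity is pO2, OE pO2 if it is TBR. At patient level with n = 20, the chance that the opposed pair exceeds +0.7 is effectively zero for true |rho| from 0.7 to 0.99, against 0.54 to 1.00 when aligned.

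This rests on the meaning of pO2, on the plan's own HTV thresholds for the direction of rOEF and TBR, and on literal use of the stated scales. It does not extend to a claim that the sign is wrong under every possible analysis, since a biomarker-specific pairing or a sign reversal would avoid it. Nor does it show that the study is underpowered: N = 19 reproduces, and the two-tailed test detects either direction equally.

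**What to change.** Reconcile sections 2.1, 2.7.4 and 2.10 by naming, before analysis, the PET quantity (TBR or pO2) to be correlated with each MRI biomarker. Which one to use is the investigators' choice; the existing choice of pO2 in section 2.7.4 can stand. Then do one of the following:

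- orient all measures so that higher means more hypoxic (for example, use minus pO2) and keep r > 0.7; or
- state the expected sign for each pair, with r > 0.7 where the scales agree and r < −0.7 where they oppose.

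An undirected |r| > 0.7 should not be used, because it would also credit a strong correlation in the wrong direction.

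The cost is a few sentences in sections 2.3.1, 2.7.2, 2.7.4 and 2.10, with the wording of 2.1 brought into line. No new data are needed and the sample size does not change.

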#### PET imaging protocol

2.7.3

At multiple timepoints determined in the study design (i.e. pre-op, once prior to commencement of chemoradiation and at suspected recurrence) the patients will also undergo a [^18^F]MISO PET/CT scan. Patients will be requested to come to the department 2 hours prior to the scan session. The amount of [^18^F]MISO given will be 370 MBq administered intravenously approximately 90 min prior to imaging. The PET data will be reconstructed to provide trans-axial images using standard protocols and the lesion uptake will be evaluated.

#### PET imaging analysis

2.7.4

PET data will be reconstructed with CT data acquired simultaneously. To quantify the radioactivity concentrations in the PET images as standardised uptake values (SUV), raw PET images will be decay corrected to the point of tracer injection using a fluorine-18 half-life of 109.77 min. PET images will be co-registered to the MRI images acquired at the same timepoint of the study via rigid co-registration of the simultaneously acquired CT image to the T_2_ map. This way the ROI delineated on the T_2_ image can be applied to the PET SUV image and be used for quantification of lesion [^18^F]MISO uptake. The primary measures to quantify lesion [^18^F]MISO uptake will be maximum standardised uptake value (SUV_max_) and tumour-to-background ratios (TBR). TBR images will be derived by normalisation of the SUV image by the mean SUV value calculated in a region of interest delineated in the contralateral healthy brain. The HTV will be defined by all voxels within the tumour ROI with a TBR ≥ 1.2 - threshold value shown to optimally distinguish hypoxic tumour from normoxic brain tissue at 90 min post tracer injection in a previous GBM study (45) – and DSC MRI-derived CBF>0 – indicating well-perfused tissue. Hypoxia levels in voxels belonging to the HTV will be measured by values of pO_2_ derived from TBR values using the above mentioned approach used by Chakhoyan et al. (35).

Finally, to facilitate the assessment of spatial and quantitative voxel-wise correlations in HTV and in levels of tumour hypoxia defined by the different imaging biomarkers, [^18^F]MISO TBR images will be resampled into the spatial resolution of the MRI image with the highest resolution by linear interpolation of voxel-wise intensity values.

#### Preparation and administration of [^18^F]MISO

2.7.5

Fluorine-18 will be sourced from a local PET radiopharmacy (Cyclotek NSW, Lucas Heights, Sydney). [^18^F]MISO will be synthesized on-site at RNSH using the ABX Products PE-SC-12, PE-TBA-001.750, PE-VVIAL-016 and the SCINTOMICS GRP^®^ Synthesizer. Cartridge purification will be carried out as part of the automated synthesis procedure programmed by Scintomics and ABX. ITLC and HPLC quality controls will be carried out post-synthesis and prior to release for patient administration. The pass mark for both HPLC and ITLC is >95%. The average QC results achieved for radiotracers produced at the RNSH facility are >98%. Following purification and characterisation procedures, a diagnostic dose of approximately 370 MBq ± 10% of [^18^F]MISO will be administered to patients via intravenous injection.

### Data collection, storage, confidentiality and retention

2.8

There will be general information recorded about the patient including patient size (height and weight).

The following radiographic and radiotherapy-specific data will be collected for each patient:

MRI images as DICOM series and raw k-space data in the proprietary vendor format[^18^F]MISO PET and CT data and reconstructed images as DICOM seriesRadiotherapy planning contoursRadiotherapy treatment plansClinical data including progression-free survival and overall survival

Patients enrolled in the study will receive a trial ID. The data saved for the trial will be under this de-identified trial ID. A separate key of the subject study number and their medical record number will be securely stored by the clinical trials staff to allow re-identification if necessary. This master list for re-identification will remain at RNSH. Only the clinical trials staff will have the ability to re-identify subjects. The data will be stored for 15 years as per Good Clinical Practice (GCP) guidelines. Imaging and clinical outcome data will be transferred from RNSH to the University of Sydney using a password protected cloud-based file share solutions from Citrix ShareFile, in accordance with the study site’s ethics and security allowances and protocols. The de-identified data will be stored for 15 years at the University of Sydney on a secure, password protected backed up storage drive (Research Data Storage). Only non-identifiable data may be made available for other scientific research, e.g., nonidentifiable data placed on a well-controlled university site, upon request. The data sharing platform is a secure on-line storage solution (“CloudStor”) provided through the University of Sydney. The data will be stored as a password-protected, encrypted file. In order to download or decompress the data, participating researchers will agree to the terms of use for the data, including that the data is not to be published or otherwise redistributed without the express consent of the original investigators.

